### **8.3.2 Per protocol analysis**

All patients who were diagnosed with CAP and received treatment according to study protocol will be included in the per protocol analysis.

Patients will be considered as non-evaluable if they fulfil the following criteria:

1. Study medication discontinued earlier than planned or less than 80% of study drugs taken.
2. Received concomitant systemic antibiotics for intercurrent illnesses.
3. No visit at evaluation point, unless subject was previously deemed a treatment failure.
4. Patients admitted to ICU
5. Death within the first 3 days of treatment.

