### **8.4.4 Clinical response analysis**

Clinical response to therapy will be assessed by the investigator at day 30. Clinical response will be based on the global assessment of the clinical presentation of the subject made by the investigator at the evaluation time point compared to the baseline assessment. Clinical outcome by the end of treatment will be cure, improvement, or failure. A clinical outcome of "cure" or "improvement" is considered a success. At the visit on day 30, the clinical outcome will be defined as successful, failure or relapse according to criteria specified in Appendix B.

"Intent to treat" and "evaluable" clinical analyses will be performed comparing clinical outcomes as defined on day 30. Ninety-five percent (95%) confidence intervals on the difference between the treatment groups in the rates of clinical success will be computed.

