## ***Appendix B: Definition of clinical and radiological responses***

### **Clinical response**

#### *Test of cure*

Cure —resolution or improvement of symptoms and clinical signs related to pneumonia without the need for additional or alternative antibiotic therapy

Failure —persistence or progression of all signs and symptoms of the acute process after randomisation or the development of a new pulmonary or extrapulmonary respiratory tract infection, or the progression of abnormalities on chest radiograph after randomisation, or death due to pneumonia, or the inability to complete the study owing to adverse events

Indeterminate —patient receives less than 80% of the study drug for reasons other than clinical failure, a concomitant infection outside the respiratory tract requiring antibiotic treatment, lost to follow-up, or death unrelated to the primary diagnosis

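### Per-protocol rule 2 can remove from the evaluable comparison patients whom Appendix B counts as failures

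*Protocol*

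**What the plan says.** Section 8.3.2 introduces its list of exclusions with "Patients will be considered as non-evaluable if they fulfil the following criteria". Rule 2 reads "Received concomitant systemic antibiotics for intercurrent illnesses". Rule 3 reads "No visit at evaluation point, unless subject was previously deemed a treatment failure". Rule 3 therefore protects known failures and rule 2 does not.

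Appendix B, under Test of cure, includes in Failure "the development of a new pulmonary or extrapulmonary respiratory tract infection". Its Indeterminate category includes "a concomitant infection outside the respiratory tract requiring antibiotic treatment". Under Late follow-up, a respiratory tract infection arising in a patient already cured is a Recurrence, and an infection outside the respiratory tract is again Indeterminate.

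Section 8.4.4 plans two versions of the clinical response comparison, intent-to-treat and evaluable: "clinical analyses will be performed comparing clinical outcomes as defined on day 30". It asks for 95% confidence intervals on the difference in success rates and refers to Appendix B for the outcome criteria, as does section 6.5.1. No sentence says which rule prevails when a patient meets both rule 2 and the Failure definition.

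**The concern.** Appendix B divides treated infections by site: inside the respiratory tract they count against the strategy, outside it they are set aside. Rule 2 makes no such division. Where the two overlap, an outcome event becomes a reason to leave the analysis of that outcome.

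The direction matters in this trial. Section 2.1 asks whether antibiotic duration can be reduced safely, and safety will be argued from a small or absent difference in clinical success. Removing failures from a comparison read in that way tends to reassure. Section 3 states that there is no blinding, and neither intercurrent nor concomitant is defined. Staff who know the arm would therefore decide whether a given course falls under rule 2.

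**Working it through.** **Step 1: the rules side by side**

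| Patient | Appendix B | Rule 2, read literally | Conflict? |
|---|---|---|---|
| Infection outside the respiratory tract, concomitant systemic antibiotics | Indeterminate | Removed | No |
| New respiratory infection, systemic antibiotics alongside the study course | Failure | Removed | Yes |
| New respiratory infection, antibiotics begun after the study course ended | Failure, or Recurrence if already cured | Depends on what concomitant means | Possible |
| Persistence, progression or return of the index pneumonia | Failure, or Recurrence if already cured | Not naturally an intercurrent illness | Not clear |

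The conflict is certain in the second row, open in the third, and not established in the fourth.

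**Step 2: what can be calculated**

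The protocol gives no failure rate, no rate of new respiratory infection and no margin for clinical success, so there is no planned figure to reproduce. The only input taken from it is 156 patients per group (section 8.1; section 4.4 prints 148, but only 3 × 156 gives the stated total of 468). All event counts and failure rates below are assumptions.

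*Same share of failures removed in both arms.* With failure rate p and share q removed, the evaluable failure rate is p(1 − q)/(1 − pq). Assume p = 10% in control and 15% in a guided arm, a true difference of 5.0 points:

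- q = 25%: 11.7% − 7.7% = 4.0 points
- q = 50%: 8.1% − 5.3% = 2.8 points
- q = 75%: 4.2% − 2.7% = 1.5 points

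The difference shrinks without any imbalance in the share removed.

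*Removal from one arm only.* Assume 16/156 failures in control and 24/156 in a guided arm, a difference of 8/156 = 5.1 points. Removing x failures from the guided arm alone gives (24 − x)/(156 − x) − 16/156, which is 4.0, 2.9, 1.7 or 0.6 points for x = 2, 4, 6 or 8. Removing 4 from control alone gives 24/156 − 12/152 = 15.4% − 7.9% = 7.5 points, which is wider. The direction therefore depends on where the removals fall.

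*Only the treated new respiratory infections differ.* Assume 16 other failures per arm, plus g such infections in a guided arm and c in control, all removed. The all-patient difference is (g − c)/156. The evaluable difference is 16/(156 − g) − 16/(156 − c).

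| g, c | All patients (points) | Evaluable (points) |
|---|---|---|
| 2, 1 | 0.64 | 0.07 |
| 4, 2 | 1.28 | 0.14 |
| 6, 2 | 2.56 | 0.28 |
| 8, 3 | 3.21 | 0.35 |

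The share of the difference that survives is 16 × 156/((156 − g)(156 − c)), between 10.5% and 11.0% here. That is close to the assumed background failure rate, 16/156 = 10.3%, whatever g and c are.

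**Step 3: scale**

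The 95% half-width for a difference in success is 1.96 × √(2p(1 − p)/156): 7.9 points at 85% success and 6.7 points at 90%. The largest loss in the last table is 3.21 − 0.35 = 2.9 points.

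**The case against.** The strongest reply is that rule 2 is shorthand for the Indeterminate category. Rules 1 to 3 run parallel to it (under 80% of study drug, a concomitant infection, no follow-up), and both texts use the word concomitant. On that reading nothing conflicts. It is a sensible reading and may be what was meant, but rule 2 does not state it and an analyst applying the text would not be bound by it.

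Several stronger inferences are tempting and do not stand:

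- A reader might infer that rule 2 deletes the failures an early stop would chiefly cause. Those are persistence or return of the index pneumonia. Section 2.2 defines relapse separately, and such a patient does not naturally have an intercurrent illness.
- A reader might infer that losses fall mainly on the guided arms, because those patients stop sooner and would need a fresh course. A course begun after study treatment ended is arguably not concomitant. If the word requires overlap, the longer control course could produce more removals in control. The planning means in 8.1 (5.13, 6.28 and 8.76 days) leave about 24.9, 23.7 and 21.2 antibiotic-free days out of 30, ratios of only 1.17 and 1.12 to control. The 2:1 to 3:1 event ratios in the last table are therefore not derived from the protocol.
- A reader might take the loss of about 90% in that table as a finding. It follows from the assumed background rate and from removing every such event.

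The affected analysis is also supportive: sections 4.4 and 8.1 make intent-to-treat duration primary, and 8.4.4 includes an intent-to-treat clinical comparison. That limits the consequence but does not remove the conflict. An analysis plan not shown here might settle precedence, but the point concerns a rule the protocol does state and that disagrees with its own outcome definition.

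**Conclusion.** The point holds in a narrow form. Read literally, rule 2 removes from the evaluable day-30 comparison some patients whom Appendix B counts as failures: those given concomitant systemic antibiotics for a new respiratory tract infection. This can bias that comparison towards no difference, and does so when the share removed is similar in both arms or larger in the arm with more failures. The amount is unknown. The illustrations rest wholly on assumed rates, and in the last table the shift stays below the half-width of the confidence interval, so nothing here shows that a conclusion would reverse. The intent-to-treat analyses of duration and clinical response keep these patients and are unaffected.

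**What to change.** Reconcile rule 2 with Appendix B and rule 3, keeping the word concomitant. For example: *Concomitant systemic antibiotics received for an infection outside the respiratory tract, unless the subject was deemed a failure or relapse according to Appendix B.* Appendix B failures then stay in the evaluable set as failures. Section 8.4.4 speaks of relapse where Appendix B says Recurrence, so the new sentence should make clear that the two are the same category. A short definition of concomitant (overlapping the study course, or any time up to day 30) would settle the open third row of the table.

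The cost is one or two sentences in 8.3.2, with no new data and no change to patient care. The evaluable success rate may become slightly less favourable, and the retained patients also enter the per-protocol duration comparison. The change should be made before the evaluable set is determined, since in an open trial the reading could otherwise be chosen with outcomes in view.

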## **8.4 Methods of analysis**

### **8.4.1 General statistical considerations**

All data will be collected and analysed using SPSS statistics 20.

Statistical analysis will be performed on an intent-to-treat basis by an independent statistician. All continuous variables will be tested for normal distribution with the Kolmogorov-Smirnov test for normal distribution. The Student-t test will be used for normally distributed variables, the Mann-Whitney U test for not normally distributed variables and the  $\chi^2$  test for dichotomous variables. The software package SPSS 20 for Windows (IBM-SPSS Inc., Chicago, Illinois, USA) is available for statistical analysis. A value of  $p < 0.05$  will be considered significant.

All data will be collected and analysed using SPSS statistics 20.

Clinical response will be analysed by using the Kruskal wallis test.

Duration of treatment and in-hospital stay will be expressed as means with a 95% confidence interval. Sub-group analyses will be performed on patients with severe CAP according to the CURB criteria and patients with non-severe CAP.

### **8.4.2 Comparison of baseline characteristics**

Baseline comparison of the treatment groups with regard to demographic variables (such as age, gender, number of co-morbidities, smoking, alcohol use, etc.) and severity of the disease.

Severity of disease will be assessed using the CURB-65 score.

### **8.4.3 Efficacy analyses**

The primary efficacy analysis will be duration of antibiotic treatment.

The secondary efficacy analyses will be clinical response on day 30, length of hospital stay, time to clinical stability, relapse rate and overall mortality on day 30 and day 90.

Possible confounders (e.g. co-morbidities, type of pathogen etc.) will be assessed. Where appropriate a correction will be performed.

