### **2.2 Secondary objective(s)**

The secondary objectives of this study are to assess the length of hospital stay, clinical response, 30-day mortality, time to clinical stability and relapse rate within 30 days. A relapse is defined as new or worsening symptoms indicative of pneumonia after initial improvement on therapy. Furthermore several biomarkers and genetic polymorphisms for corticosteroid-receptors will be assessed at the end of the study.

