## **3. Study design**

This study will be set up as a Randomised Controlled Trial with a parallel design, patients will be randomly allocated to one of 3 treatment groups. No blinding will be performed, since treating physicians will have to make a decision to continue or withhold treatment based on laboratory evaluations. In order to make the right decision they will have to know whether or not the patient is receiving antibiotics.

Patients will be included at hospital admission and the follow up period is 1 month. The control group will consist of patients getting treated according to common clinical practice.

Patients will be admitted to hospital and receive therapy according to the study protocol. They will be discharged from the hospital when their medical condition and social situation is stable. If patients are discharged and still using antibiotics, blood tests will be performed daily in the participating centre and the researcher will contact the patients by phone to inform them whether or not antibiotic treatment can be discontinued. After discharge the patient will be evaluated at an outpatient visit on day 30. In case of any event an interim visit will be scheduled. If for some reason a patient fails to perform an outpatient blood test, antibiotics will be continued until the next blood test or for a total of 7 days and the reason for failure will be documented.

This study will be conducted in the Medical Centre Alkmaar, the Isala clinics in Zwolle and the Slotervaart hospital in Amsterdam.

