## **6.3 Study procedures**

All diagnostic and other procedures are outlined in appendix C, a distinction is made between common clinical practice and extra procedures patients will undergo if they choose to participate in this study.

Subjects will be evaluated for clinical stability every day of hospitalization. Laboratory evaluations will be performed for hospitalised patients at day 1 and days 3-7 until the threshold level is reached. Any laboratory evaluation after day 7 will be on indication. Microbiological evaluations will be determined at baseline and if applicable on day 30. An outpatient visit will be scheduled at day 30. A detailed overview of the different procedures is outlined below.

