### ***10.5 End of study report***

The investigator will notify the accredited METC of the end of the study within a period of 8 weeks. The end of the study is defined as the last patient's last visit. In case the study is ended prematurely, the investigator will notify the accredited METC within 15 days, including the reasons for the premature termination. Within one year after the end of the study, the investigator/sponsor will submit a final study report with the results of the study, including any publications/abstracts of the study, to the accredited METC.

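### Section 8.4.3 lists day-90 mortality, but follow-up stops at day 30 and no later vital-status check is planned

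*Protocol*

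**What the plan says.** Section 8.4.3 (Efficacy analyses) ends its list of secondary efficacy analyses with "relapse rate and overall mortality on day 30 and day 90". No other section mentions day 90.

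The sections that fix what is collected, and until when, stop at day 30:

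- Section 3 (Study design): "Patients will be included at hospital admission and the follow up period is 1 month", and "After discharge the patient will be evaluated at an outpatient visit on day 30".
- Section 2.2 (Secondary objectives) lists "clinical response, 30-day mortality, time to clinical stability and relapse rate within 30 days". Section 6.1.2 repeats the same list.
- Section 6.3 (Study procedures): "An outpatient visit will be scheduled at day 30". In the detailed overview (6.4) the last entry is 6.4.5, the day-30 visit, and the last column of Appendix C is day 30.
- Section 6.7 follows withdrawn patients, where possible, on the same schedule.
- Section 10.5: "The end of the study is defined as the last patient's last visit". On the schedule given, that is the last patient's day-30 visit.

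**The concern.** The analysis section commits the trial to an outcome that the data-collection sections do not provide for. A statistical analysis plan could say how day-90 mortality is to be analysed, but it would not by itself add a contact, extend follow-up or move the end of the study. The protocol fixes those.

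The primary objective is to show that antibiotic treatment can be shortened safely as well as effectively, in an unblinded trial. Mortality is one of the few hard outcomes bearing on safety, so readers will give a listed mortality result weight. If the text stays as it is, two outcomes are likely. Day-90 mortality may be reported from whatever deaths happened to become known, or it may be dropped without comment, leaving a listed outcome unreported. Either is easily avoided.

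**Working it through.** The protocol gives no expected day-90 mortality, so there is no figure of its own to reproduce on this point. The check sets the sections side by side and then works through the timeline.

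**Step 1. Is there a planned contact after day 30?**

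| Place in the protocol | Latest time point |
|---|---|
| 2.2 and 6.1.2, mortality | day 30 |
| 3, length of follow-up | 1 month |
| 6.3, 6.4.5 and Appendix C, last scheduled visit | day 30 |
| 6.7, withdrawn patients | same schedule, so day 30 |
| 8.4.3, mortality analysis | day 90 |

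Appendix B has response categories for a late follow-up, but it gives them no date and no entry in the schedule corresponds to them. They do not create a day-90 contact.

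**Step 2. Length of the gap.** 90 − 30 = 60 days, or 60/90 = two thirds of the stated window. No scheduled visit falls in it for any of the 468 planned patients. This is a calendar gap and does not estimate how many deaths would be missed.

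**Step 3. What could still pick up a death in days 31 to 90?** Section 7.3 makes death a serious adverse event, and section 7.4 requires such events to be reported until the end of the study. Section 10.5 defines that end for the trial as a whole, not for each patient. So the reporting duty outlasts a patient's own day-30 visit by an amount that depends on when the patient enrolled.

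Let *T* be the enrolment date of the last patient and *e* that of any other patient.

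- End of study = *T* + 30.
- The patient's day 90 = *e* + 90.
- Day 90 falls on or before the end of study if *e* + 90 ≤ *T* + 30, that is, if *T* − *e* ≥ 60.
- The reporting window, capped at day 90, closes on day min(90, 30 + (*T* − *e*)).

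| Enrolled before the last patient by | Window closes on day |
|---|---|
| 0 days | 30 |
| 30 days | 60 |
| 60 days or more | 90 |

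So for patients enrolled less than 60 days before the last one, the reporting duty stops before their day 90. The protocol gives no recruitment period, so their share of the 468 cannot be calculated. If accrual were even over *R* days, it would be about 60/*R*.

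For everyone enrolled earlier, the duty covers day 90, but no planned contact prompts it. A death counts only if someone tells the investigators.

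**Step 4. Does this touch the primary analysis?** No. The primary outcome is duration of antibiotic treatment, and the sample size in sections 4.4 and 8.1 rests on a 2-day difference and standard deviations of that duration. Mortality does not enter it.

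**The case against.** The best reply is that vital status does not need a visit. Section 10.1 has the sponsor keep a list linking study numbers to patients, and study data are kept for 15 years, so a records search or a telephone call could supply day-90 status later. Deaths are also reportable to the end of the study, which for most patients may fall after their own day 90, and section 7.4 follows adverse events until they resolve or stabilise, with no cut-off at day 30. Finally, handling of missing status is commonly left to a statistical analysis plan, which may exist.

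Much of this stands, and it rules out several stronger readings that a reader might infer:

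- *That day-90 mortality cannot be measured.* The documents do not support this. It could be obtained; the protocol plans no step to obtain it.
- *That patients without information would be counted as alive, so that mortality is understated.* The protocol states no such rule.
- *That the loss would differ between arms because the stopping strategies change readmission.* This is possible, but the protocol offers neither a figure nor a statement to support it.
- *That each patient's reporting closes at day 30.* Section 10.5 sets a trial-level date, as step 3 shows.

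The contradiction remains. The ability to find out later is not a plan to do so. Passive reporting is incomplete, and its window varies with enrolment date. Continued follow-up of adverse events reaches only patients who have one unresolved.

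**Conclusion.** The point holds as an internal contradiction. Section 8.4.3 lists a day-90 outcome, while the objectives, follow-up period and visit schedule stop at day 30. With the procedures described, deaths in days 31 to 90 would be captured only passively. For patients enrolled in the final 60 days, even that route closes early.

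Day-90 mortality would thus be incompletely ascertained. The number of deaths missed cannot be estimated from the protocol, and the direction of any bias between arms is unknown. The conclusion assumes that the last patient's last visit is the day-30 visit, as the schedule implies, and that no separate document arranges a later status check.

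The effect is limited to one time point of one secondary outcome. Thirty-day mortality, the primary outcome and the sample size stand.

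**What to change.** Reconcile the text in one of two ways, according to whether the sponsor wants a day-90 result.

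1. **Delete the day-90 time point from section 8.4.3.** This brings it into line with 2.2, 3 and 6.1.2 and needs no new data. It does remove a listed outcome, so it should be made as a recorded amendment under section 10.3. It also gives up the later mortality time point.
2. **Plan the measurement.** Add one day-90 vital-status check, by records or telephone, for all randomised patients, including those who stopped treatment early. Enter it in sections 2.2, 3, 6.1.2, 6.4 and Appendix C, and align the end-of-study definition in 10.5. Record the date of death, or the date on which the patient was last known to be alive. Check that consent covers the contact or records search; the consent forms are not in the file at hand.

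The second option costs one small task per patient, at most 468 in all. It also moves the end of the study back by about 60 days, and with it the end of serious adverse event reporting under 7.4 and the notification and report deadlines in 10.5.
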